### Study population

The study population is defined as all adult patients with a non-displaced distal radius fracture. All patients should be independent in activities of daily living. Evaluation of eligible patients will take place either at the emergency department or at the outpatient department of the Spaarne Hospital, Hoofddorp. Patients are eligible using the following in- and exclusion criteria:

### Inclusion criteria

1. Age > 18 years.

2. Unilateral fracture of distal radius without misalignment (dorsal angulation <15°, Axial radial shortening <5 mm.

3. Independent for activities of daily living.

### Exclusion criteria

1. Fracture of contralateral arm.

2. Other fractures at the ipsilateral arm (excluded carpal fractures).

3. Pre-existent abnormalities fractured distal radius.

4. Open fractures.

5. Fracture that needs reduction.

### Study procedures

After inclusion, all patients will be followed for one year in total. Clinical assessments will occur at the time of admission (ED), one week (3-10-day window), three weeks (11-28-day window) or five weeks (4-8-week window), six weeks (4-8-week window), three months (11-15-week window), six months (5-7-month window), and 12 months (12-14-month window) after start of treatment.

At each FU visit, the research coordinator or research assistant will ascertain patient status (i.e., secondary interventions, adverse events/complications, deaths) and will verify information within medical records.

At each FU visit, the patients will be asked to indicate the pain level on a VAS.

At each visit from six weeks onwards, the ROM of the wrist will be measured using a goniometer by a doctor blinded for the treatment method. In addition, patients will be asked to complete the questionnaires relating to disability (Quick-DASH score including optional modules, PRWE Score), and healthcare consumption.

Plain X-rays of the wrist will be made at the time of presentation in the hospital (ED), and at the follow-up visit after 6 weeks three months, six months and one year. The X-ray at 12 months will be taken in order to determine the grade of degenerative joint changes.

Time to define the presence of a malunion will be at three months. Intention-to-treat principle will be maintained (see Figure 2).

X-ray: control X-ray according to standard guidelines, assessment using Lidström score [19].

Function: functional assessment using functional outcome scores, range of motion, pain assessment using VAS scale.

ED = Emergency Department, D = days, W = weeks, M = months.

### Sample size

The primary outcome will be the QuickDASH score of which the minimal clinically important difference is 14 points. Based on a difference of 14 points, the sample size of 30 patients per treatment group was calculated with a power (1-β) of 80 percent and a type I error (α) of 5 percent, allowing for 10 percent drop-out. In total 70 patients will be included.

### Withdrawal of individual subjects

Subjects can leave the study at any time for any reason if they wish to do so without any consequences. The investigator can decide to withdraw a subject from the study for urgent medical reasons.

### Statistical analysis

#### *Descriptive statistics*

Data from the demographic data collection and the outcome parameters will be cleaned blindly from the treatment data. Data are presented as mean scores with 95% confidence intervals.

#### *Univariate analysis*

The analysis of this study will be carried out according to the intention-to-treat principle, i.e. the patients will remain in the group they will be randomly allocated to at baseline. Analysis of functional outcome will be assessed using repeated-measures analysis of variance (GLM 4) with the time as the within-group factor and the treatment as the between-group factor. Post-hoc analysis will be performed on the time of randomization. Group comparisons at the different time points will be made only when the overall repeated-measures tests are statistically significant. All scores will be tested for normality using the Kolmogorov-Smirnov test. Parametric variables will be compared using the Student’s t-test, while non-parametric and ordinal variables will be compared using the Mann–Whitney U statistic. Nominal variables will be compared across independent groups using the chi-squared test or Fisher’s exact test. Homogeneity of variance will be assessed using Levene’s test. Also a multiple regression will be performed. SPSS statistical software (version 11.0.1) will be used for the analysis, in which two-tailed P value < 0.05 will be considered significant.

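### The one-year comparison is gated by a repeated-measures ANOVA that needs all four questionnaires, so patients with a valid one-year score can be lost from the deciding test; a mixed model would keep them

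*Protocol article*

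**What the plan says.** The Univariate analysis section fixes the method for the functional scores: "Analysis of functional outcome will be assessed using repeated-measures analysis of variance (GLM 4) with the time as the within-group factor", with treatment as the between-group factor. It then sets a gate: "Group comparisons at the different time points will be made only when the overall repeated-measures tests are statistically significant". The abstract places the primary outcome, PRWE and QuickDASH, at one year, so the one-year comparison lies behind that gate.

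Study procedures supplies the repeated measurements. In the paragraph on visits from six weeks onwards it says: "In addition, patients will be asked to complete the questionnaires relating to disability". The scheduled visits from that point are six weeks and three, six and twelve months, which makes four scores per patient.

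The same analysis section states: "The analysis of this study will be carried out according to the intention-to-treat principle". It explains this as meaning that "the patients will remain in the group they will be randomly allocated to at baseline". The only loss figure is in the Sample size section, where 30 per group and 70 in total are given "allowing for 10 percent drop-out". The article names no mixed model, imputation or other way to keep a patient with an incomplete series in the ANOVA.

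**The concern.** Repeated-measures ANOVA in its classical form works on one complete row of scores per patient. If one of the four is missing, the row is not used. A patient who skips the three-month form but attends at one year contributes nothing to the overall test, although the primary score is on file.

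The gate makes this matter for the primary result. If the overall test fails, the one-year comparison is not made at all, and the overall test is decided by completers only. Two things are at stake:

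- **Information.** Observed scores are discarded, including one-year scores.
- **Bias.** If the chance of missing a later visit depends on earlier scores, and does so differently by arm, the completers in the two arms are no longer comparable.

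This is a consequence of the method the article chose, not of a detail it left out.

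**Working it through.** **Inputs from the article.** 70 patients, 1:1; four questionnaire visits; target difference 14 QuickDASH points; 80% power; two-sided alpha 5%; 10% drop-out.

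**Assumptions.** No SD, missed-visit rate or between-visit correlation is given. Missed-visit rates of 5% and 10% per visit, independent between visits, are used for illustration.

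**1. The plan's own figure.** The 30 per group cannot be reproduced without an SD. Solving backwards, 30 per group implies SD 19.35 by the normal approximation or 19.03 by the t-test. If the 30 already include drop-out, so that 27 are analysed, the SD is 18.36. The step to the total does reproduce: 30 / 0.9 = 33.3, rounded up to 34 per group, or 68, within two patients of 70.

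**2. Patients with a complete series.** With rate m missed at each of four visits, the complete share is (1 − m)^4.

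| Scenario | One-year score present | Complete series | One-year score present, but outside the ANOVA |
|---|---|---|---|
| 10% drop-out only | 70 × 0.90 = 63 | 63 | 0 |
| 5% missed per visit | 70 × 0.95 = 66.5 | 70 × 0.95^4 = 57.0 | about 9 to 10 |
| 10% drop-out, plus 5% missed at each of the three earlier visits | 63 | 70 × 0.90 × 0.95^3 = 54.0 | 9 |
| 10% missed per visit | 63 | 70 × 0.90^4 = 45.9 | about 17 |

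The calculation needs 60 complete patients. They are retained as long as (1 − m)^4 is at least 60/70 = 0.857, that is, up to about 3.8% missed per visit.

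**3. Power of a single-time-point t-test.** For 14 points at SD 19.03, power is 82% with 63 patients, 78% with 57, 76% with 54 and 68% with 46. At SD 18.36 it is 85%, 81%, 79% and 72%. These figures relate the counts to the sample size calculation. They are not the power of the ANOVA.

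**4. Power of the ANOVA's between-group test.** This test compares the mean over four visits. With equal correlation ρ between visits, the SD of that mean is 19.03 × √((1 + 3ρ)/4). At ρ = 0.6 this is 19.03 × √0.70 = 15.92. For a constant 14-point difference and 23 per group, power is 87%, 83%, 79% and 75% at ρ = 0.5, 0.6, 0.7 and 0.8. At 27 per group it is 92% down to 82%. A difference that fades over time would lower these values.

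**5. ANOVA against an all-available-data model.** A simulation used 1,500 trials of 70 patients, SD 19.35, ρ = 0.6 and random missingness, with a true difference of 10 points (not the planned 14). Power was 62% for the complete-case test and 73% for the mixed-model estimate at 5% missed per visit, and 53% against 72% at 10%. The mixed-model estimate used the known covariance, which flatters it slightly.

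**6. Bias in an adverse case.** The same set-up was run with no true effect. Later visits were missed depending on the six-week score, in opposite directions in the two arms. The complete-case estimate was off by 4.8 points with a type I error of 21% (base rate 5%), and by 8.2 points with 45% (base rate 10%). The mixed-model estimate had bias near zero and a type I error of about 5% in both. This mechanism was chosen to be unfavourable and nothing in the article predicts it. It shows what can happen, not what will.

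**The case against.** The strongest reply is that the article nowhere says incomplete patients will be deleted. An analysis plan not shown could impute before the ANOVA, and missing-data detail is commonly left to that plan. This stands as a limit: the absence of such detail is no finding. The criticism is of the method and gate that the article does fix, for which a better alternative can be named.

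The reply is also right that the only documented loss, 10% drop-out, leaves 63 complete patients and about 82% power even on the single-time-point test. Any shortfall comes from assumed intermittent missed visits.

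Some stronger readings are tempting but unsupported:

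- **That the plan contradicts its intention-to-treat statement.** The article explains the principle only as patients staying in their allocated group, and deletion moves nobody between arms. What remains is that a deleted patient is analysed in no arm.
- **That the safety comparison is biased.** Complications are a separate secondary outcome, and nominal variables go to a chi-squared or Fisher's exact test. A missed questionnaire removes nobody from those.
- **That patients with complications will be withdrawn and then deleted.** The withdrawal section says only that "The investigator can decide to withdraw a subject from the study for urgent medical reasons". It does not name complications, and Study procedures has them recorded at each follow-up visit.
- **That power falls to 68%.** That is a t-test figure at one time point under 10% missed per visit. Step 4 gives the corresponding ANOVA values.
- **That the F tests will be too liberal for lack of sphericity.** The article does not say they will be uncorrected, and the treatment main effect does not depend on sphericity. In null simulations with autoregressive correlation of 0.6 to 0.8, the uncorrected interaction test rejected in 6.0% to 6.7% of trials, which is a small excess.

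**Conclusion.** The point holds in a limited form. Followed as written, the plan lets a complete-series test decide whether the one-year comparison is made, and patients with a valid one-year score but one missed questionnaire do not count in that test. This falls short of analysing all randomized patients.

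With 5% to 10% missed independently per visit, 57 to 46 of 70 patients have a complete series, and about 9 to 17 patients with a one-year score are left out. Those rates are assumptions. Below about 4% per visit, or with only the planned drop-out, the 60 patients the calculation needs are still there. The possible bias is real in principle, but its size depends on a missingness mechanism that the article gives no means to judge. The case for change is that a method using all observed scores is available at little cost, not that the trial as planned is shown to be underpowered.

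**What to change.** In the Univariate analysis section, replace the repeated-measures ANOVA by a linear mixed model for repeated measures, fitted to all available QuickDASH scores of all randomized patients in their allocated group, and likewise to PRWE. Include treatment, visit and treatment-by-visit, with an unstructured covariance over the four visits, REML estimation and Satterthwaite degrees of freedom. State that the 12-month treatment contrast from this model, with its 95% confidence interval, is the primary comparison and does not depend on an overall test. Contrasts at the other visits then become secondary. The unstructured covariance also removes the sphericity assumption, a minor gain.

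The cost is a few sentences and no extra patients or visits. The model is slightly more complex: four variances and six covariances are estimated. It relies on missing at random and does not cure missingness that depends on unobserved scores. The article names SPSS 11.0.1 for the analysis and does not show whether that version fits this model, so the software should be confirmed when the text is changed.

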### Recruitment and consent

Patients with distal radius fractures will be initially managed on the emergency department. Using the criteria for displacement: distal radial fractures with initial dorsal angulation up to 15° and axial radial shortening of not more than 5 mm. Patients will be included if closed reduction of the distal radius fracture is not necessary according to these criteria for misalignment.

They will receive written information and a consent form from the attending physician, the clinical investigator or a research assistant. After providing informed consent, eligible patients will be randomized within one week. An independent research assistant will perform concealed permuted block randomization using a computer-generated randomization schedule after stratification for fracture type, gender and age. Allocation will be at random to four blocks.

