### Bias prevention

To prevent bias stratification by age (younger and older than 60 years) and gender will be performed (Table 1).

**Table 1 T1:** Stratification by gender and age (younger and older than 60 years)

	**Patient characteristics**		**Randomization**
List 1	Male	Median age -	ABAB AABB ABBA BABA BAAB
List 2	Male	Median age +	BAAB BBAA ABAB AABB ABBA
List 3	Female	Median age -	AABB ABBA BAAB BBAA BABA
List 4	Female	Median age +	ABBA BABA ABAB AABB AABB

A = 3 weeks, B = 5 weeks.

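### The functional-outcome model omits the factors used to stratify randomization, so the test of the treatment effect is conservative to the extent that those factors predict QuickDASH or PRWE

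*Protocol article*

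**What the plan says.** The Bias prevention section states: "To prevent bias stratification by age (younger and older than 60 years) and gender will be performed". Table 1 there gives four lists, gender by age group, in blocks of four with two patients per arm. The first Recruitment and consent section describes "concealed permuted block randomization using a computer-generated randomization schedule after stratification for fracture type, gender and age", which adds fracture type, a factor that Table 1 does not contain.

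The Univariate analysis section sets the analysis of functional outcome as a repeated-measures analysis of variance with time as the within-patient factor "and the treatment as the between-group factor". Comparisons at single time points follow only if the overall repeated-measures tests are significant, and use Student's t-test or the Mann–Whitney test, also without covariates. One further sentence reads "Also a multiple regression will be performed". It names no outcome, no covariates and no role.

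In the Sample size section, "The primary outcome will be the QuickDASH score of which the minimal clinically important difference is 14 points". The figures there are 30 patients per group, 80% power, 5% type I error, 10% drop-out and 70 patients in total.

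**The concern.** The design and the model do not match. Stratified permuted blocks keep the arms nearly balanced on the stratification factors, so those factors contribute almost nothing to the true sampling variance of the treatment difference. A model with treatment as its only between-patient term still counts their variation as error. The reported standard error then exceeds the true one.

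Three features make this worth a line of text. The trial is small. Study procedures schedules the questionnaires from the six-week visit onwards, so no baseline QuickDASH or PRWE score is planned for adjustment, and gender and age are the prognostic candidates already at hand. And because time-point comparisons, including the one-year result, depend on a significant overall test, a conservative overall test can prevent them from being made.

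**Working it through.** **The plan's own figure.** The article gives no standard deviation, so 30 per group can only be solved backwards: SD = 14 × √(30/2) / (1.960 + 0.842) = 19.35 if 30 are evaluable. If the 30 already includes 10% drop-out, 27 are evaluable and the SD is 18.36. Adding drop-out to 30 gives 30/0.9 = 33.3, so 34 per group, against the 70 planned in total. The choice does not affect what follows: in each case the SD is set so that an unadjusted test without stratification has 80% power, that is, a standardised effect of 1.960 + 0.842 = 2.80.

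**Inputs.** Two-sided 5% test and 80% power (article); 1:1 allocation in blocks of four (Table 1); R², the share of outcome variance explained by the stratification factors (assumed, 0 to 0.30).

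**Formulas**, normal approximation, for a between-patient treatment effect or a single visit:

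- Ratio of true to reported standard error, unadjusted model: √(1 − R²).
- True type I error, unadjusted: 2 × [1 − Φ(1.96/√(1 − R²))].
- Power, unadjusted, in the stratified trial: Φ((2.80 − 1.96)/√(1 − R²)).
- Power, adjusted: Φ(2.80/√(1 − R²) − 1.96).
- Factor k by which the unadjusted trial must grow to match adjusted power. Setting (2.80√k − 1.96)/√(1 − R²) equal to 2.80/√(1 − R²) − 1.96 gives √k = [2.80 + 1.96(1 − √(1 − R²))]/2.80.

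Example at R² = 0.10: √0.90 = 0.949. Type I error is 2 × [1 − Φ(2.066)] = 3.9%. Unadjusted power is Φ(0.842/0.949) = 81.3%. Adjusted power is Φ(2.802/0.949 − 1.960) = 84.0%. √k = (2.80 + 1.96 × 0.051)/2.80 = 1.036, so k = 1.07.

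| R² (assumed) | True/reported SE | True type I error | Power unadjusted | Power adjusted | Gain, points | k |
|---|---|---|---|---|---|---|
| 0 | 1.00 | 5.0% | 80.0% | 80.0% | 0 | 1.00 |
| 0.05 | 0.975 | 4.4% | 80.6% | 82.0% | about 1 | 1.04 |
| 0.10 | 0.949 | 3.9% | 81.3% | 84.0% | about 3 | 1.07 |
| 0.20 | 0.894 | 2.8% | 82.7% | 87.9% | about 5 | 1.15 |
| 0.30 | 0.837 | 1.9% | 84.3% | 91.8% | about 7 | 1.24 |

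**Simulation check.** Stratified blocks of four, 60 patients, 6000 runs per scenario, SD 19.35, one endpoint. Assumed stratum shares were 12%, 13%, 30% and 45% (younger men, older men, younger women, older women), with equal gender and age effects. At R² = 0.05, 0.10 and 0.20:

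- Unadjusted type I error was 4.5%, 3.9% and 3.0%; adjusted, it was 5.0%, 4.7% and 5.2%.
- Power, unadjusted against adjusted, was 79.4% v 80.6%, 79.5% v 82.4% and 81.8% v 87.5%.
- At R² = 0.20 the true standard error of the unadjusted difference was 4.48, against a mean reported value of 4.98.

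**Which test is affected.** A stable difference between men and women, or between age groups, sits in the between-patient error. It cancels within each patient and so does not enter the error for treatment-by-time. The table therefore does not carry over to the interaction unless the factors also change the course of recovery.

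**The case against.** **It is a matter for the analysis plan.** A condensed article may leave covariate lists to a fuller document, and the multiple regression could turn out to be the adjusted analysis. This stands in part: the text does not rule it out. But the article names the factors of its functional-outcome model, and the regression is introduced as an addition with no stated content. As written, it does not bring the stratification factors into that test.

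**The effect is hypothetical.** This stands. The article does not say how strongly gender or age predicts QuickDASH or PRWE, and with R² = 0 nothing is lost.

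**The harm is small.** This also stands. A reader might set adjusted power of 84–88% against the planned 80%, and take 1/(1 − R²) to mean 11–25% more patients at R² of 0.10–0.20. That overstates the power gain, because stratification already lifts the unadjusted test to 81.3–82.7%; in power terms the gain is worth about 7–15% more patients. The ratio 1/(1 − R²) does describe interval width.

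**The article does not name the decisive test.** It refers to overall repeated-measures tests without saying whether treatment or treatment-by-time governs. A reader might infer that the whole repeated-measures analysis loses power. Only the between-patient effect and single-visit comparisons do so automatically.

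A reader might also infer a biased or invalid trial. The documents do not support that: the unadjusted estimate is unbiased and the error is on the conservative side.

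**Conclusion.** The point holds as a conditional loss of efficiency. The mismatch between stratified randomization and a model with only time and treatment is in the text. Its consequence depends on an R² that the article does not supply: for 5–20%, about 1–5 points of power and reported standard errors about 3–12% too large, falling to nothing if the factors are not prognostic. These figures assume near-complete balance within strata, a between-patient or single-visit comparison, and an SD that makes the planned 80% power true. The change is worth making because it is nearly free; its absence does not threaten validity.

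**What to change.** First reconcile the Recruitment and consent section with the Bias prevention section and Table 1 on whether fracture type is a stratification factor. Confirm the age cut at the same time, since the title of Table 1 gives 60 years while its rows are labelled by median age.

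Then state that the factors actually used in randomization enter the primary repeated-measures model as between-patient terms, for both QuickDASH and PRWE, and are carried into the follow-up time-point comparisons. Keep the unadjusted result as a sensitivity analysis, and say whether the multiple regression serves any other purpose.

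The cost is one line of text and a few degrees of freedom: two for gender and age group, plus one fewer than the number of categories if fracture type is included. Gender and age are already among the baseline data listed under Outcome measures. Fracture type is not in that list, so its recording should be confirmed if it is a factor.

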**Methods/Design:**

The aim of the study is to evaluate whether the duration of immobilization of non or minimally displaced distal radial fractures can be safely reduced. We will compare three weeks of plaster cast immobilization with five weeks of plaster cast immobilization in adult patient with non or minimally displaced distal radial fractures.

Study design: a prospective randomized clinical trial.

Study population: adult (>18 years) (independent in activities of daily living) patients with a non/minimal displaced distal radius fracture (dorsal angulation <15°, volar tilt <20°, radial inclination >15°, ulnar positive variance <5 mm and an articular step off <2 mm).

Intervention: three weeks of plaster cast immobilization versus five weeks of plaster cast immobilization.

Main study parameters: primary outcome parameters: Patient related wrist evaluation (PRWE) Quick Disability of Arm, Shoulder and Hand (QUICKDASH) score after a one year follow-up, and secondary parameters: range of motion, pain level (VAS) and complications.

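### The one-year primary comparison may be made only after unspecified omnibus tests are significant, so the stated 80% power is at best an upper limit; a normality pre-test then chooses its method

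*Protocol article*

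**What the plan says.** - **Time point.** The abstract (Methods/Design) gives the primary parameters as PRWE and QuickDASH "score after a one year follow-up". The Outcome measures and Sample size sections do not repeat the time point.
- **Sample size.** The section takes QuickDASH as the primary outcome: "Based on a difference of 14 points, the sample size of 30 patients per treatment group was calculated", with "power (1-β) of 80 percent" and a "type I error (α) of 5 percent, allowing for 10 percent drop-out". It gives no SD, test, time point, within-patient correlation or gate.
- **Visits.** Under Study procedures, the questionnaires are completed at every visit from six weeks on: six weeks, three, six and twelve months.
- **Analysis.** Univariate analysis assesses functional outcome by repeated-measures analysis of variance, with time within and treatment between patients. It then adds: "Group comparisons at the different time points will be made only when the overall repeated-measures tests are statistically significant".
- **Choice of test.** The same section continues: "All scores will be tested for normality using the Kolmogorov-Smirnov test". Student's t-test or Mann–Whitney follows accordingly, and a "two-tailed P value < 0.05 will be considered significant".

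**The concern.** One year is one of the time points covered by the gating sentence. Read literally, the plan can forbid the comparison that the abstract calls primary, even when the assumed 14-point difference is real. The sentence speaks of tests in the plural and does not say whether the treatment test, the treatment-by-time interaction, either one or both must be significant. The choice matters: a difference that is the same at every visit produces no interaction, and one that appears only late produces little treatment main effect.

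The sample-size statement shows no sign that its 80% allows for this step. In addition, if the one-year comparison is reached, its method is picked from the data. Mann–Whitney does not test the mean difference on which the 14-point threshold is defined.

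**Working it through.** **1. The plan's own figure.** Inputs from the Sample size section: difference 14, power 80%, α 5% (two-sided per Univariate analysis), 30 per group. No SD is given, so the 80% cannot be reproduced directly; the SD can only be solved for.

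- Normal approximation: SD = 14 × √(30/2) / (1.960 + 0.842) = 14 × 3.873 / 2.802 ≈ 19.35.
- Exact t-test: the detectable standardised difference is 0.7356, so SD = 14 / 0.7356 ≈ 19.03.
- If 30 already includes drop-out, leaving 27 evaluable, the SD is 18.0 (exact t) to 18.4 (normal approximation).
- Drop-out: 30 / 0.9 = 33.3, so 34 per arm; 60 / 0.9 = 66.7, so 67 in total. The planned 70 covers this.

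The stated size therefore fits a single ungated two-group comparison with an SD of about 19.

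**2. Direction of the gate's effect.** P(gate passed and one-year test significant) ≤ P(one-year test significant). This holds whatever the SD, correlation or effect profile.

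**3. Size of the effect.** Simulation, 4,000 trials per cell, 30 per arm, normal data, SD 19, equal correlation ρ between four visits. The group test and the interaction test (Greenhouse–Geisser) form the gate, followed by a t-test at 12 months. The SD, ρ and profiles are assumptions; every profile has 14 points at 12 months. Entries are the percentage of trials that pass the gate and are significant at 12 months.

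| Difference at 6 wk, 3, 6, 12 mo | ρ | No gate | Group | Interaction | Either | Both |
|---|---|---|---|---|---|---|
| Constant: 14, 14, 14, 14 | 0.3 | 78.8 | 78.6 | 3.0 | 78.7 | 3.0 |
| | 0.5 | 80.2 | 79.5 | 3.4 | 79.5 | 3.4 |
| | 0.7 | 80.8 | 79.3 | 2.8 | 79.4 | 2.7 |
| Growing: 3.5, 7, 10.5, 14 | 0.3 | 80.3 | 66.2 | 28.8 | 73.1 | 21.8 |
| | 0.5 | 80.3 | 58.2 | 38.4 | 70.9 | 25.7 |
| | 0.7 | 80.0 | 50.6 | 55.6 | 72.9 | 33.3 |
| 12 months only: 0, 0, 0, 14 | 0.3 | 79.2 | 17.2 | 61.9 | 67.1 | 12.0 |
| | 0.5 | 79.7 | 13.8 | 71.4 | 73.7 | 11.6 |
| | 0.7 | 80.0 | 13.0 | 79.0 | 79.3 | 12.7 |
| Fading: 25, 20, 16, 14 | 0.3 | 79.2 | 79.2 | 22.8 | 79.2 | 22.8 |
| | 0.5 | 79.7 | 79.7 | 35.2 | 79.7 | 35.2 |
| | 0.7 | 80.0 | 80.0 | 55.0 | 80.0 | 55.0 |

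The simulation error is at most √(0.25/4000) ≈ 0.8 points (standard error). Repeat simulations moved the ranges by no more than about 2 points; one gave 69–80% instead of 67–79% for the 12-months-only profile with either test. With 27 per arm and SD 18.0, the growing and 12-months-only profiles behave in the same way.

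**4. The normality pre-test.** Simulation with 30 per arm and a Lilliefors-type test in each arm, then t-test or Mann–Whitney:

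- Normal data, 14-point shift: power 79.9% with selection, 80.1% for the t-test alone. Type I error is 4.5% and 4.6%.
- Right-skewed (gamma) data, 14-point shift: power 83–95% with selection, 80–81% for the t-test. Normality is rejected in at least one arm in 46–95% of trials.
- Exponential data with means 12 and 26, hence unequal spread: 71% with selection, 81% for the t-test.

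The switch can raise or lower power, but under skewness the data often decide which test is used.

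**The case against.** The strongest defence is that the repeated-measures model is itself the main analysis of functional outcome, and that the visit-by-visit tests are protected follow-ups, a conventional guard against multiplicity. That reading is possible, since the Sample size section names neither a test nor a time point. It does not remove the problem: the abstract would then name a one-year endpoint that the analysis section treats as a conditional follow-up, and the two would still need reconciling. Nor does a single pre-specified one-year comparison need that protection: with no true difference, the ungated test was significant in 5.0–5.6% of simulated trials.

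A second objection stands in part. The Background expects a shorter cast to hasten recovery, which points to an early effect; a difference that appears only at 12 months is the least plausible profile and should carry little weight. For a constant or fading effect with a gate that the group test can open, the loss is under 2 points. The plan does not say that this is the gate, however, and if both tests are required the fading profile gives only 23–55%.

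Third, the Descriptive statistics section presents means with 95% confidence intervals, so arm means stay available whichever test is used. That is fair, but it does not fix which test decides the primary question.

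Three stronger readings might be inferred and are not supported:

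- **That the 80% is wrong.** Without an SD, correlation or effect profile in the document, it is shown only to be a ceiling.
- **That the normality pre-test erodes power.** It does so only in some settings, and in others raises it.
- **That an early difference that has vanished by one year would be mistaken for a one-year result.** Such a difference merely opens the gate, and the one-year test is then made.

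**Conclusion.** The concern holds in a limited form. The plan makes its one-year primary comparison conditional on omnibus tests that it does not identify, and does not reconcile this with the abstract. That the gate cannot raise power follows from logic alone. How much it costs depends on assumptions: from almost nothing (constant or fading effect, group test sufficient), through about 7–9 points (growing effect, either test sufficient), to near-total loss (constant effect, interaction or both required). The SD of 19 is solved from the stated n and power. The correlations and profiles are illustrative, and the four visits are counted from the visit schedule, because the label GLM 4 is not defined.

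The Kolmogorov-Smirnov switch is a separate and lesser fault: the primary test and the effect it addresses are left to the data.

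**What to change.** - **Univariate analysis:** state that the primary test is the between-arm difference in mean QuickDASH at 12 months, with its 95% CI, two-sided at 0.05, estimated from the repeated-measures model and carried out whatever the omnibus tests show.
- **Other visits:** make them secondary. The gate may stay for these, provided the text names the test or tests that open it.
- **Normality switch:** drop it for this outcome, and report a bootstrap CI for the same mean difference as a sensitivity analysis for skewness.
- **Abstract, Outcome measures and Sample size:** align them on 12 months as the time point and on QuickDASH as the outcome the trial is sized for, since PRWE is also listed as primary. State the SD behind 30 per group.

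The cost is small wording edits in several sections. No patients or data are added.
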